### Primary Outcome

The primary outcome being assessed is an increase in FEER. This will be measured by comparing the percent of correctly identified facial emotion expressions from the baseline assessment task to the instructed mimicry experimental task. Additionally, the percent of correctly identified expressions will also be compared between the control condition and the intervention condition. This will provide 2 primary metrics: before-after percent improvement and control group to experimental group percent improvement.

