### Intervention

The task will be delivered in-person at the Federation University Psychology Clinic in Ballarat, Australia, by the primary author in a small counselling room. The room will have 2 computers on a desk, each with separate monitors and peripherals (one for the participant and the other for recording eye-tracking data). Participants will take part in the task 1 participant at a time based on a mutually agreed upon time and date. Participants will only undergo this task once, and it is expected to take approximately 30 minutes based on prior testing where a small neurotypical group took approximately 25 minutes to complete the task in a usability test. The intervention is a software-based FEER training task that presents a series of different facial expressions and requires individuals to firstly mimic and then select which emotional expression they saw. The software runs on Microsoft Windows 10 and requires only minimal system requirements and a mouse.

The intervention task condition will begin with the software presenting a basic description of 6 facial expressions (fear, sadness, happiness, anger, disgust, surprise) and tips on how to spot each expression. Next, participants will be verbally advised by the experimenter and by on-screen text that a series of emotion recognition trials will begin shortly. Further, they will be told that after each emotion is displayed that they should try their best to mimic (copy) the observed facial expression with their own face. Once they have mimicked the expression, they should then use the 6 labelled buttons on the right-hand side (or associated keyboard shortcut) to choose which emotion was displayed. After selecting the answer using 1 of the 6 buttons, a 5-point Likert scale on the computer screen will ask the participant “How well did you mimic the expression?” with responses ranging from 1 “not very well” to 5 “very well.” This will repeat for each of the 36 trials. The trials will include various models of both men and women depicting the 6 emotions.

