The sequence of each trial in the task is depicted in Figure 2 with accompanying numbered indexes. Each trial will begin with a neutral expression image displayed on the screen (index 1). After this image has been displayed for 3 seconds, it will quickly swap to another image from the same model, except this image will depict an emotional expression (eg, angry or sad, index 2). After 500 milliseconds, this image will be replaced with the original neutral image (index 3), and the 6 buttons with emotion labels will appear on the right-hand side (index 4). Once the participant selects the emotion using the 6 buttons, the trial will conclude with the 5-point rating of how well the participant felt they copied the expression (index 5).

In a task that aims to test or train FEER ability, it is important to ensure that the emotional stimuli tested against are true exemplars of the emotion they purport to signal. It is also important that the expressive images in the baseline test and the experimental tasks are similar in recognition difficulty. This will reduce the risk of improvements being attributed to easier expressions in the experimental tasks compared to the baseline task. This task used the Warsaw Set of Emotional Facial Expression Pictures (WSEFEP) [57]. See Multimedia Appendix 3 for a description of these pictures and how pictures were selected for each condition. See Figure 2 for an example of the pictures.

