### Comparator/Control Group

This study includes both a before-after, within-group comparator and a between-groups control group. To make the before-after comparison, participants will first partake in a baseline assessment task of emotion recognition before randomization to one of the experimental conditions. This baseline assessment task will be the same as the intervention task; however, participants will not be instructed to mimic the facial expressions prior to selecting an expression.

In addition to the before-after comparator, there will be a control condition. The control condition will also undergo the baseline assessment task; however, instead of participating in the mimicry intervention task, they will undergo a similar task with no mimicry element. This task will be identical to the instructed mimicry intervention task; however, instead of being instructed to mimic the facial expression, they will be instructed to “pay particular attention to the entire face prior to selecting an expression.” This instruction is aimed to match for attention levels.

A final point of comparison will be that participants will be first broken up into 2 groups, namely the AM group and ASD group. This comparison will provide the ability to analyze if any intervention effects only occur or are stronger in people with ASD, alexithymia, or the general population. The participant flow diagram can be seen in Figure 3.

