## Appendix

Multimedia Appendix 1 Workflow of participants through in-person segments of study.

Multimedia Appendix 2 Questionnaire of Task Satisfaction.

Multimedia Appendix 3 Selection process of pictures to match task difficulty between the baseline task and the experimental task.

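### If, as the text implies, the baseline and experimental tasks use different fixed picture sets, any leftover difficulty gap passes in full into the before-after primary metric

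*Protocol article*

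**What the plan says.** The Primary Outcome section of the protocol article measures improvement by "comparing the percent of correctly identified facial emotion expressions from the baseline assessment task to the instructed mimicry experimental task", and continues: "This will provide 2 primary metrics: before-after percent improvement and control group to experimental group percent improvement". Study Aims also lists change from baseline to posttest as part of the first aim. Statistical Analyses says the mixed ANOVA will judge whether the mimicry task worked by setting posttest scores against baseline scores.

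On the pictures, the Intervention section states: "It is also important that the expressive images in the baseline test and the experimental tasks are similar in recognition difficulty". It says of the matching: "This will reduce the risk of improvements being attributed to easier expressions in the experimental tasks compared to the baseline task". For detail it refers the reader on: "See Multimedia Appendix 3 for a description of these pictures and how pictures were selected for each condition". The Appendix list titles that file "Selection process of pictures to match task difficulty between the baseline task and the experimental task".

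The only factor named under Randomization is the task condition. The ANOVA in Statistical Analyses has time, group and condition, with IQ, depression and anxiety as covariates. It has no term for picture set or set order.

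**The concern.** The stated risk, that the experimental pictures are easier than the baseline pictures, has a direction. It can arise only if particular pictures belong to particular tasks. If the sets were swapped between participants, neither task could be systematically easier.

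When each set belongs to one time point, set difficulty and time cannot be separated within an arm. An easier experimental set would look like improvement, and a harder one would hide it. A larger sample does not help: the bias stays the same size while the test becomes more likely to call it significant. At stake is one of the two primary metrics, which the plan reads as evidence of efficacy.

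**Working it through.** **Inputs from the article.** Each task has 36 trials (Intervention: "This will repeat for each of the 36 trials"), so one picture is worth 100/36 = 2.78 percentage points. The required sample is 58 (Sample Size Calculation). Arms are equal, so the mimicry arm has 58/2 = 29.

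**Assumptions.** The article gives neither the SD of the change score nor the gap left after matching. I take an SD of 8 to 12 points, a gap d of 1 to 2.78 points, no true change and no practice effect.

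**The plan's own figure.** The article gives no number for set difficulty. Its sample size does reproduce: f² = 0.27, 5% significance and the six predictors of Table 3 give N = 58 with power 0.808, and 58 × 1.10 = 63.8, rounded to 64. This point does not change it.

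**Step 1: bias.** Let δ be the true change and d the amount by which the experimental set is easier.
- Mimicry arm, fixed sets: expected change = δ_M + d.
- Control arm, same sets: expected change = δ_C + d.
- Between-arm difference: (δ_M + d) − (δ_C + d) = δ_M − δ_C.

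The gap enters the before-after change with coefficient 1 and cancels between arms. Neither result depends on the assumed SD or gap. The cancellation does require both experimental tasks to use the same pictures, which Comparator/Control Group supports: "This task will be identical to the instructed mimicry intervention task; however, instead of being instructed to mimic the facial expression".

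**Step 2: how often the before-after test would be falsely significant.** Take a two-sided 5% paired t-test with n = 29, 28 df and noncentrality d√n/SD. With d = 2.78, d√n = 2.78 × 5.385 = 14.96.
- SD 8: noncentrality 1.87, significant in 43.9%.
- SD 10: noncentrality 1.50, significant in 30.4%.
- SD 12: noncentrality 1.25, significant in 22.6%.

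Smaller gaps matter less. In the same SD order, d = 2 gives 25.5%, 18.0% and 14.0%, and d = 1 gives 10.0%, 8.2% and 7.2%. With the full recruited arm of 32 and d = 2.78, the rates are 47.7%, 33.1% and 24.5%.

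**Step 3: effect of counterbalancing.** Call the sets A and B. Participants taking A then B have expected change δ + d, and those taking B then A have δ − d. With equal halves the mean is δ, and half the difference between the two orders estimates d. A simulation (40,000 runs, n = 32 split 16/16, d = 2.78, SD 8 and 10) gave a mean bias of about 0 and false-positive rates of 3.8% and 4.2% without order in the model. With fixed sets the rates were 48.0% and 33.2%. The between-arm test with fixed sets stayed at about 5%.

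**The case against.** The strongest objection is that no sentence says the sets are fixed. A reader might take it as established that counterbalancing was rejected, but the article does not support that. It leaves picture selection to an appendix that is not shown, and an article's silence proves little. This stands, and it makes the point conditional. What remains is the article's own wording: pictures chosen by condition, and a one-directional risk that would not exist under counterbalancing. Comparator/Control Group does call the baseline task the same as the intervention task apart from the mimicry instruction. Read with the matching statement, that means the same procedure; matching difficulty would be pointless with identical pictures.

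Second, the authors name the threat, match the sets and claim only to reduce the risk. That is fair. No document figure suggests that a one-picture gap survives matching, and nothing in the article shows that matching fails in ASD or alexithymia. The percentages are therefore illustrations.

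Third, the control arm already protects the main test. The efficacy hypothesis under Hypotheses compares improvement between conditions, and none of the five hypotheses is an uncontrolled before-after test. A reader might infer that the trial's efficacy result as a whole is biased, which would be wrong. But Primary Outcome still declares the before-after change a primary metric, and the control arm does not protect it.

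Fourth, counterbalancing would not make the before-after change a clean measure of efficacy, because a similar task is repeated and practice remains. This also stands, and it shapes the fix.

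Finally, it is tempting to run the illustration on all 58 participants, which gives higher rates. That would not describe the declared metric, which Primary Outcome defines on the mimicry task.

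**Conclusion.** The point holds conditionally and is a minor one. As the article reads, matched but task-specific picture sets are the likely arrangement, to be confirmed against Multimedia Appendix 3. If so, any remaining difficulty gap biases the before-after primary metric by exactly its own size, in either direction, and leaves the between-arm contrast unbiased.

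For scale, a one-picture gap would make the mimicry-arm before-after test significant in about 23% to 44% of trials at n = 29, against a nominal 5%. That range rests on the assumed gap and SD, on no true change and on no practice effect. The one-for-one pass-through needs none of these.

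**What to change.** First check Multimedia Appendix 3. If it already describes counterbalancing, one sentence in the Intervention section settles the matter.

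If it does not, treat the two matched 36-picture sets as A and B. Assign the order (A then B, or B then A) from a pre-generated list before the baseline task, balanced within the ASD and AM groups. Comparator/Control Group places baseline before randomisation, so the order cannot simply be drawn with the arm in the existing blocks. Either balance the task arms across order at randomisation, or randomise arm and order together and conceal the arm until baseline is complete. Add set order and its interaction with time to the mixed ANOVA.

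In either case, rest the efficacy claim on the between-arm difference in change and report the before-after change as supportive, because practice effects remain.

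The cost is a software switch and one more balancing factor on top of age, gender and group. Cells fall from about 16 to about 8 (64/8). A few degrees of freedom are lost: crossing order with group and condition doubles the between-subject cells from 4 to 8, which costs 4. Timeline says recruitment had not begun as of June 2021, so the change was feasible on the document's own schedule.

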**Figure 2 figure2:**
[figure not shown]
Task sequence and stimulus example.

### Comparator/Control Group

This study includes both a before-after, within-group comparator and a between-groups control group. To make the before-after comparison, participants will first partake in a baseline assessment task of emotion recognition before randomization to one of the experimental conditions. This baseline assessment task will be the same as the intervention task; however, participants will not be instructed to mimic the facial expressions prior to selecting an expression.

In addition to the before-after comparator, there will be a control condition. The control condition will also undergo the baseline assessment task; however, instead of participating in the mimicry intervention task, they will undergo a similar task with no mimicry element. This task will be identical to the instructed mimicry intervention task; however, instead of being instructed to mimic the facial expression, they will be instructed to “pay particular attention to the entire face prior to selecting an expression.” This instruction is aimed to match for attention levels.

A final point of comparison will be that participants will be first broken up into 2 groups, namely the AM group and ASD group. This comparison will provide the ability to analyze if any intervention effects only occur or are stronger in people with ASD, alexithymia, or the general population. The participant flow diagram can be seen in Figure 3.

**Figure 3 figure3:**
[figure not shown]
Participant flow diagram. ASD: autism spectrum disorder; K-10: Kessler Psychological Distress Scale.

### Randomization

Participants will be randomized using permuted block randomization with stratification across age and gender to receive either the control or experimental task condition with equal numbers from both the ASD group and AM group receiving each task.

### Sample Size Calculation

Based on the effect sizes of 2 previous studies measuring similar constructs and similar tasks [32,35], to achieve a medium to large effect (eg, Gpower f^2^ test = 0.27) with a significance of 5% (*P*=.05) and power of 80%, a sample size of 58 will be required to demonstrate statistical significance for the primary hierarchal regression and analysis of variance (ANOVA). Given an expected attrition of 10%, a total of 64 participants will be recruited.

### Statistical Analyses

The data will be analyzed using SPSS, Version 25. Alexithymia will be analyzed to aid in matching the AM group and ASD group on alexithymia. To ensure that the ASD and AM groups, and also the experimental and control groups, are comparable, means and standard deviations of participant characteristics will also be compared with tests of difference.

The study design is a mixed factor, 2x2x2, within-between design (see Table 2), and therefore, the most appropriate test of difference is a mixed factorial ANOVA, set up according to Table 2 with IQ, depression, and anxiety variables added as covariates. This will provide analyses of whether the instructed mimicry intervention task was effective by comparing baseline scores to posttest scores. Additionally, it will provide the ability to compare posttest scores between the control group and the intervention group. Finally, this analysis will have the additional ability to discern these differences based on group (ASD group and AM group).

In addition to the mixed factorial ANOVA, a hierarchical regression analysis will also be conducted (see Table 3) to determine the predictive ability of alexithymia on the primary outcome variable.

**Table 2 table2:** Experimental group and intervention design.

Time point	ASD^a^ group (n=~32)		AM^b^ group (n=~32)	
	Control task condition (n=~16)	Mimicry task condition (n=~16)	Control task condition (n=~16)	Mimicry task condition (n=~16)
Pretest	FEER^c^ task score	FEER task score	FEER task score	FEER task score
Posttest (the intervention task is the posttest)	FEER task score	FEER task score	FEER task score	FEER task score

^a^ASD: autism spectrum disorder.

^b^AM: alexithymia-matched general population.

^c^FEER: facial emotion expression recognition.

**Table 3 table3:** Hierarchal regression stages for analysis.

Stage	Variables
Stage 1	IQ, age, gender
Stage 2	+Autism
Stage 3	+Alexithymia
Stage 4	+Intervention

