### Assessments

The main aim of the current study is to assess the efficacy of the intervention in the general population and an ASD population, but also if people with high levels of alexithymia gain additional benefit. Further, this study will aim to replicate the study by Cook et al [32], which suggested that alexithymia, not ASD, predicts poor FEER. This requires having a general population group and another group with people with ASD, with both groups being matched on levels of alexithymia. Therefore, participants will be prescreened online to facilitate creating this composition of participants. During the online screening stage, participants will choose to consent in the study, complete the TAS-20, and indicate if they have an ASD or if they have been diagnosed with an ASD. During this screening stage, participants will also complete demographic information, the Autism Spectrum Quotient (AQ-10) [42], and the K-10.

Participants will then be invited to a clinical interview with a provisional psychologist (PP) at the Federation University Psychology Clinic who will confirm a reported diagnosis of ASD and complete an observational assessment that gives a diagnostic indication of an ASD. Participants who have reported a diagnosis will be asked what instrument was used and if the PP can request a copy of the results. The PP will also complete the Autism Mental Status Exam 2.2 (AMSE) [43,44]. The AMSE is an 8-item observational assessment that takes place during a clinical interview and predicts ASD classification on the Autism Diagnostic Observation Schedule (ADOS) [45]. During this clinical interview, participants will also be administered the Depression Anxiety Stress Scales-21 (DASS-21) [46] and the Wechsler Abbreviated Scale of Intelligence (WASI-II) [47] to assess depression, anxiety, and IQ, which will be used as control variables in the analyses of the results.

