### Hypotheses

It is hypothesized that the condition that receives the mimicry task will show significantly better emotion recognition improvement scores (posttest minus baseline); the degree of alexithymia will negatively predict baseline scores; the degree of alexithymia will predict improvement scores (posttest minus baseline); when matched on alexithymia, the general population and ASD population will not significantly differ in emotion recognition improvement scores (posttest minus baseline); and when matched on alexithymia, the AM group and ASD group will not significantly differ on baseline emotion recognition scores.

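### The mimicry-versus-control test is a valid change-score comparison, but it does not use baseline FEER as a covariate, omits the stratification factors age and gender, and its covariates do not match those of Table 3

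*Protocol article*

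**What the plan says.** The Statistical Analyses section of the protocol article names its efficacy model and covariates outright: "a mixed factorial ANOVA, set up according to Table 2 with IQ, depression, and anxiety variables added as covariates". Table 2 makes pretest and posttest FEER the two levels of the time factor, so baseline FEER is part of the outcome and not a covariate. The section says the model will show "whether the instructed mimicry intervention task was effective by comparing baseline scores to posttest scores", and that "it will provide the ability to compare posttest scores between the control group and the intervention group". The Hypotheses section states efficacy as a difference between conditions in improvement, defined as posttest minus baseline.

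The Comparator/Control Group section places the baseline task before randomisation. The Randomization section specifies "permuted block randomization with stratification across age and gender", with "equal numbers from both the ASD group and AM group receiving each task".

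The Assessments section says the DASS-21 and WASI-II are given "to assess depression, anxiety, and IQ, which will be used as control variables in the analyses of the results". The ANOVA follows this. Table 3 does not: its Stage 1 contains IQ, age and gender, and no later stage adds depression or anxiety. Table 1 lists the BVAQ, IQ and demographics as control variables and puts the DASS-21 under eligibility.

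**The concern.** There are three linked points.

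1. **Baseline.** Every participant has a baseline FEER score taken before allocation. A change score subtracts that baseline with a fixed slope of 1. ANCOVA estimates the slope from the data. Where the true slope is below 1, the change score leaves avoidable noise in the arm comparison.
2. **Stratifiers.** Allocation is balanced on age and gender, but the ANOVA contains neither. If they predict the outcome, the variation they explain stays in the error term and the standard error does not reflect the balance obtained by design. ASD/AM group, also balanced in allocation, is already a factor in the model.
3. **Covariate sets.** The two named analyses adjust for different variables, and Table 3 departs from the Assessments section. Table 3 is the analysis of how well alexithymia predicts the outcome, so that coefficient would be left unadjusted for two variables the protocol says it will control.

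What is at stake is precision in a trial with about 32 participants per arm, and agreement between the protocol's own statements about its controls.

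**Working it through.** **Inputs.** From Sample Size Calculation: f² = 0.27, alpha 0.05, power 80%, 58 evaluable, 10% attrition, 64 recruited. From Table 2: about 16 per cell. From Table 3: six predictors (IQ, age, gender, autism, alexithymia, intervention). The correlation rho between baseline and posttest FEER is not in the protocol, so it is assumed over a range.

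**The plan's own figure.** With the noncentral F test of an overall regression (noncentrality f² × N, 6 and N − 7 degrees of freedom), f² = 0.27 and six predictors require N = 58 (power 0.808). Then 58 × 1.10 = 63.8, rounded to 64. The stated size therefore matches the overall test of the Table 3 regression. It uses no rho and so gives no information on the precision of the ANOVA contrast.

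**Planned test and ANCOVA.** Let the pretest and posttest SDs be s0 and s1.

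- Change score: residual variance s0² + s1² − 2·rho·s0·s1.
- ANCOVA on baseline: residual variance s1²(1 − rho²).
- Difference: (s0 − rho·s1)², which is never negative.

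With s0 = s1 = 1 these become 2(1 − rho) and 1 − rho², and the ratio of ANCOVA to change score is (1 + rho)/2.

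| rho (assumed) | Change 2(1 − rho) | ANCOVA 1 − rho² | Ratio | 58 × ratio | ANCOVA power if planned test has 80% at N = 58 |
|---|---|---|---|---|---|
| 0.3 | 1.40 | 0.91 | 0.65 | 37.7 | 93.5% |
| 0.5 | 1.00 | 0.75 | 0.75 | 43.5 | 89.9% |
| 0.7 | 0.60 | 0.51 | 0.85 | 49.3 | 85.9% |
| 0.8 | 0.40 | 0.36 | 0.90 | 52.2 | 83.9% |
| 0.9 | 0.20 | 0.19 | 0.95 | 55.1 | 81.9% |

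The fifth column is the number of participants ANCOVA needs to match the precision of 58 analysed by change score. The power column allows for the one degree of freedom spent on baseline.

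**Simulation check.** This used 4,000 runs with N = 64, a true effect of 0.5 SD, the four-cell design and three non-prognostic covariates in every model.

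| rho | Planned model | + baseline | + baseline and two non-prognostic covariates |
|---|---|---|---|
| 0.3 | 35% | 50% | 48% |
| 0.5 | 49% | 60% | 58% |
| 0.7 | 69% | 75% | 74% |

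The last column stands in for age and gender with no predictive value at all. Their cost can be read from the SDs of the simulated estimates: (0.249/0.244)² = 1.04 at rho 0.3, (0.229/0.225)² = 1.04 at 0.5 and (0.186/0.183)² = 1.03 at 0.7. So the variance rises by about 3 to 4% if they explain nothing. The simulated covariates were not balanced between arms, as stratified factors would be.

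**Degrees of freedom at N = 58.** The planned contrast has an intercept, group, condition, their interaction and three covariates: 58 − 7 = 51. Adding baseline, age and gender as one term each leaves 58 − 10 = 48.

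**The case against.** The strongest reply is that nothing here is an error. The time-by-condition test addresses the hypothesis as written, is unbiased under randomisation and keeps its type I error. That stands. A reader might infer that the efficacy test is invalid or that baseline is ignored, and the protocol supports neither: baseline is the pretest level of the time factor, and the loss is one of efficiency only.

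A reader might also conclude that the mixed ANOVA should be dropped. It should not. It supplies the before-after metric of the Primary Outcome section and the ASD-versus-AM comparisons of baseline and improvement in the Hypotheses section. Those groups are not randomised, so conditioning on baseline would change the question being asked.

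Nor is a raw posttest comparison shown to be the primary test. The protocol mentions it as something the model makes possible, while its outcome and hypotheses are framed as improvement.

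The size of the gain is uncertain. The two tasks are nearly identical, given in direct succession, with pictures chosen for similar difficulty, so rho above 0.7 cannot be excluded. At 0.8 to 0.9 the variance saving is only 10 to 5%. The gain from age and gender is unproven, because the protocol does not say how prognostic they are.

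Finally, Table 3 answers a different question and may reasonably hold different variables. That is true in general, but the Assessments section promises depression and anxiety as controls without excepting this analysis.

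**Conclusion.** The point holds as a low-cost improvement in efficiency and a matter of consistency, not as a fault in validity. For the randomised contrast, ANCOVA has smaller residual variance than the planned change-score test at every rho below 1 when pretest and posttest variances are equal. The factor is 0.65 at rho 0.3, 0.75 at 0.5, 0.85 at 0.7, 0.90 at 0.8 and 0.95 at 0.9. Which of these applies cannot be settled from the protocol. Rho here is the correlation within groups after the other covariates.

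Age and gender improve precision only if they are prognostic. The firmer reason to include them is that the analysis then matches the stratified design. The difference between Table 3 and the Assessments section is a plain inconsistency, whatever rho may be.

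**What to change.** 1. For the mimicry-versus-control contrast, prespecify an ANCOVA of posttest FEER on condition, ASD/AM group, their interaction, baseline FEER, age, gender, IQ, depression and anxiety. Code group so that the condition effect is averaged over ASD and AM. Using improvement as the outcome with baseline as a covariate gives the same condition coefficient, so the hypothesis need not be reworded. Do not read the group coefficient of this model as the ASD-versus-AM comparison.
2. Keep the mixed ANOVA, without baseline as a covariate, for the before-after metric and the ASD-versus-AM comparisons of baseline and improvement. Say which model answers which hypothesis.
3. Add depression and anxiety to Table 3 Stage 1, and align Table 1's list of control variables with the Assessments section.

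**Cost.** All variables are already collected, and the Timeline section says recruitment had not begun as of June 2021. The ANCOVA uses about three further degrees of freedom (51 to 48 at N = 58). Table 3 grows from six to eight predictors. If f² stays at 0.27, the overall regression test then has power 0.745 at N = 58 and needs 64 evaluable, which the sample-size text should acknowledge. A test of one predictor with f² = 0.27 is almost unaffected (power 0.973 with six predictors, 0.972 with eight). The allocation procedure need not change.

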#### WASI-ll

The WASI-II [47] is an individual, clinician-administered measure of cognitive intelligence based on the Wechsler Adult Intelligence Scale - Fourth Edition (WAIS-IV) [54]. The WASI-II includes 4 subtests: block design, vocabulary, matrix reasoning, and similarities. It produces 3 metrics: Full-Scale IQ, Verbal IQ, Performance IQ. The WASI-II correlates highly with the WAIS-IV and has good reliability and validity [55].

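### The covariate-adjusted ANOVA is to supply the before-after test, but centring is not stated; if IQ, depression and anxiety enter as measured, that test is evaluated at IQ = 0

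*Protocol article*

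**What the plan says.** The Statistical Analyses section of the protocol article states that "The data will be analyzed using SPSS, Version 25" and specifies a "mixed factorial ANOVA, set up according to Table 2 with IQ, depression, and anxiety variables added as covariates". Table 2 has two time points, two groups (ASD and AM) and two task conditions. The section says this model will show "whether the instructed mimicry intervention task was effective by comparing baseline scores to posttest scores", and that it will also compare conditions and groups.

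The Primary Outcome section says: "This will provide 2 primary metrics: before-after percent improvement and control group to experimental group percent improvement". It defines the before-after metric as the change from the baseline task to the mimicry task. Study Aims also lists improvement from baseline to posttest in the first aim.

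IQ comes from the WASI-II ("It produces 3 metrics: Full-Scale IQ, Verbal IQ, Performance IQ"), and depression and anxiety from the DASS-21. The article does not say whether these scores enter as measured or centred, and it gives no expected mean or SD for them.

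**The concern.** With two time points, the within-subject part of this ANOVA is a regression of D = posttest minus baseline on condition, group, their interaction and the covariates. The test labelled time is the test of that regression's intercept. An intercept is the expected value when every covariate is zero. A DASS-21 score of zero is possible, but an IQ of zero lies far outside any sample.

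If the stated model is run with the scores as collected, the time line of the output does not test mean improvement. It tests an extrapolation with a very large standard error, and nothing in the label warns the reader. At stake is the inferential answer to the before-after question, which the article says this model will provide.

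**Working it through.** **The plan's own figure.** The sample size rests on "Gpower f^2^ test = 0.27", 5% significance and 80% power. An overall regression F test with the 6 predictors of Table 3 (IQ, age, gender, autism, alexithymia, intervention) gives N = 58 with power 0.808, so the stated 58 reproduces. Adding 10% gives 58 × 1.1 = 63.8, or 64. Neither figure depends on centring.

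**Standard error of the time test.** For one covariate, moving the evaluation point from the mean to zero multiplies the standard error by about √(1 + (mean/SD)²).
- IQ 100, SD 15 (assumed): √(1 + 6.67²) = √45.4 = 6.7.
- IQ 105, SD 13 (assumed): √(1 + 8.08²) = √66.2 = 8.1.

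Depression and anxiety add further terms of the same kind, so the full model does somewhat worse.

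**Simulation of the time effect.** Common assumptions, none of them in the documents: true mean change +5 percentage points, residual SD of change 10, no relation between IQ and change.

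| Scenario | SE as measured | SE centred | Ratio | Power as measured | Power centred |
|---|---|---|---|---|---|
| N = 64, IQ 100/15 (2000 runs) | 9.2 | 1.24 | 7.4 | 7% | 98% |
| N = 58, IQ 105/13 (4000 runs) | 11.8 | 1.31 | 9.0 | 6% | 96% |

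Leaving the covariates out gives practically the same power as centring (98% and 96%). The loss needs no relation between IQ and change; the distance of IQ from zero is enough.

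**Bias if change varies with IQ.** With slope b points of change per IQ point, the intercept is approximately the mean change minus b × mean IQ. At a mean IQ of 100 and a true change of +5 (N = 64):

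| b (assumed) | By formula | Simulated estimate | Significantly positive | Significantly negative |
|---|---|---|---|---|
| 0 | 5 | +4.6 | 6.6% | 0.6% |
| 0.1 | 5 − 10 = −5 | −5.3 | 0.4% | 9.0% |
| 0.2 | 5 − 20 = −15 | −15.1 | 0.1% | 35.6% |
| 0.3 | 5 − 30 = −25 | −25.1 | 0% | 75.9% |
| −0.2 | 5 + 20 = 25 | +24.8 | 74.2% | 0% |

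With centred covariates the estimate stays at about +5.0 and power at 97–98% throughout. With no true mean change and b = 0.2, the model with covariates as measured rejects in 56.5% of runs, against 6.0% centred.

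**What does not change.** Centring alters only the intercept. The time-by-condition estimate and test are identical either way (for example, rejection 0.339 in both at b = 0.2), and the time-by-condition-by-group test is unchanged for the same reason.

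**The case against.** The strongest reply is that the article never says the covariates enter uncentred, and that scaling is a detail a journal article may leave to the full protocol or analysis plan. A reader might infer that the plan has chosen uncentred covariates; the text does not support that, and the point has to stay conditional. It survives as a condition because the article names the model, the covariates and the software, and says that this combination delivers the before-after answer. Carried out literally, it does not.

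The second reply is that no listed hypothesis is a time main effect. That is correct. The first hypothesis compares improvement scores between conditions, which is the time-by-condition test. A reader might infer that the randomised comparison is compromised; it is not.

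The third reply is that the Primary Outcome section defines the before-after metric as change to the mimicry task, whereas the time main effect pools mimicry and control participants. This also stands: even a centred time main effect is not that metric. It bears on the wording of the fix and does not remove the problem, since a within-mimicry contrast evaluated at zero covariates has the same fault.

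Finally, a reader might infer that a real gain would be reported as a loss. That needs a relation between IQ and change, which the documents neither state nor quantify. A plain mean change in percent correct is not affected at all.

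**Conclusion.** The point holds in conditional form. The plan takes one of its two primary metrics from a covariate-adjusted repeated-measures model without saying that the covariates are centred. If they are entered as measured, the time test has a standard error about 7 times too large (6.7 by formula and 7.4 by simulation for IQ 100, SD 15; 9.0 for IQ 105, SD 13), and a real gain would usually be missed. Bias or reversal of sign is possible only if change also varies with IQ. The sizes rest on assumed values for IQ, gain and SD of change; that the test is evaluated at zero covariates is algebra and does not.

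The scope is narrow: the before-after test only. The comparisons of improvement between conditions and between groups, and descriptive changes, stand as planned.

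**What to change.** In Statistical Analyses, add one sentence stating that IQ, depression and anxiety are grand-mean centred before entering the ANOVA. Alternatively, state that the before-after test is taken from estimated marginal means at the covariate means, or from the model without covariates. In either case, say that the before-after contrast is the one within the mimicry condition, to match Primary Outcome.

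The cost is that sentence and a line of analysis code. The interaction tests and covariate slopes do not change, and no additional data or participants are needed.
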